### Strategies to improve adherence to interventions {11c}

Fidelity of the intervention will be assessed using the framework for behavioural interventions recommended by the National Institute of Health (NIH) [24, 25] as outlined in Table 2.

**Table 2 Tab2:** Intervention fidelity strategies (adapted)

Goal	Strategies
Training providers	Specialist Cancer Nurses will be trained to standardise the delivery of the intervention to study participants. Training includes provision of study manual containing • Generic study information: standard operating procedures, study overview, reporting and documentation guidelines, communication flowchart, rationale for the study treatment, completion of survivorship care plan, self-management goal setting, and health coaching • Specialist Cancer Nurse-specific information: job description, intervention protocol, quality assurance, and monitoring An 8-h training program will be delivered by Experts in Cancer Survivorship and motivational interviewing. The program includes the National Cancer Nursing Education (EdCAN) learning module on survivorship, related literature, didactic presentations, and roleplay covering: basic concepts of quality cancer survivorship care, components of a high-quality treatment summary and survivorship care plan; provision of self-management support (including collaborative goal setting; motivational interviewing); and MBS item numbers that facilitate the proposed Model of Care.
Delivery of intervention	Intervention procedures are monitored through completion of intervention component checklists to ensure that the intervention is delivered as intended. Intervention checklists are completed during Clinics and GP Case Conferences to track protocol deviations across Specialist Cancer Nurses and study Arms. The intervention fidelity is closely monitored and discussed during the weekly 30-min meeting for the first 3 months of the trial between the Specialist cancer Nurses, research nurses, and investigators. Minimising contamination between conditions by training interventionists to address participant questions about randomisation and their assigned condition using non-biased explanations.
Receipt of intervention	The SCP serves as a resource for a participant to understand and refer to whenever they are unsure of follow-up schedule and collaborative goal setting.
Enactment of treatment skills	Enactment of treatment skills includes processes to monitor and improve participant ability to perform treatment-related behavioural skills and cognitive strategies in relevant real-life settings as intended. This goal will be achieved by ensuring participants are aware of the follow-up schedules and responsibilities of all health professionals, ensuring participants will have a copy of the completed SCP including all care responsibilities and goals set for the individual, and checking in with participants once in the first week into the model, then monthly/bimonthly until the end of the trial period as resources allow.

### Relevant concomitant care permitted or prohibited during the trial {11d}

No concomitant care or intervention is prohibited during the trial.

### Provisions for post-trial care {30}

There is no ancillary or post-trial care for participants in this trial. However, it is expected that the SCP generated will have the value of informing longer term updates of the SCP and future survivorship care.

### Outcomes {12}

The feasibility outcomes are recruitment and acceptability of the intervention. The primary endpoint is health-related quality of life (HRQoL) as measured by Functional Assessment of Cancer Therapy—Breast Cancer (FACT-B) [26] at baseline, 3, 6, and 12 months post-enrollment. The 37-item FACT-B is a valid and reliable tool for use in cancer survivors undergoing as well as beyond treatment and has been demonstrated to be sensitive to changes over time [27]. A total score as well as scores for each of the five subscales (physical, social/family, emotional, functional wellbeing, additional breast cancer concerns) are calculated, where higher scores indicate higher quality of life. FACT-B captures key domains of HRQoL and key symptoms that are relevant to the study population and sensitive to the EMINENT intervention.

Additional outcomes include a range of patient-reported secondary endpoints, and process outcomes related to implementation as shown in Table 3. Participants of the intervention group, as well as their nominated carer, breast cancer nurses, GPs, and other healthcare providers including other nurses, and hospital- and community-based rehabilitation providers will be invited to participate in a semi-structured interview. Open ended questions (Online Supplementary Material 1) will explore key factors that facilitate or hinder the implementation of the EMINENT intervention.

**Table 3 Tab3:** Schedule for data collection during the EMINENT trial

	Study period						
	Enrolment	Allocation	Post-allocation				Close-out
Timepoint	***-t***_**1**_	***0***	***t***_**1**_	***t***_**2**_	***t***_**3**_	***t***_**4**_	***t***_***x***_
**Enrolment**							
Eligibility screen	X						
Informed consent	X						
Allocation		X					
**Interventions**							
EMINENT							
Usual Care							
**Primary endpoints**							
Health-related quality of life			**X**	**X**	**X**	**X**	
**Secondary endpoint**							
Patient experience of care			**X**				
Dietary behaviours			**X**	**X**	**X**	**X**	
Physical activity and sedentary behaviours			**X**	**X**	**X**	**X**	
Financial toxicity			**X**		**X**	**X**	
Adherence to clinical assessments							**X**
Health resource utilisation				**X**	**X**	**X**	**X**
Satisfaction of care						**X**	
Acceptance of intervention						**X**	

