**Methods:**

We describe a protocol for a phase II, randomised controlled trial with two parallel arms and 1:1 allocation. A total of 60 patients with early-stage breast cancer will be randomised to usual, specialist-led, follow-up care (as determined by the treating surgeons, medical oncologists, and radiation oncologists) or shared follow-up care intervention (i.e. EMINENT). EMINENT is a nurse-enabled, pre-specified shared-care pathway with follow-up responsibilities divided between cancer centre specialists (i.e. surgeons and oncologists) and general practitioners. The primary outcome is health-related quality of life as measured by the Functional Assessment of Cancer Therapy—Breast Cancer. Secondary outcomes include patient experience, acceptance, and satisfaction of care; dietary, physical activity, and sedentary behaviours; financial toxicity; adherence; health resource utilisation; and adverse events.

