### Trial design {8}

This phase II pilot RCT aims to assess the feasibility of a larger definitive clinical trial. Outcome data will be collected at four timepoints (or five if Booster Nurse Clinic is attended): (*t*_1_) baseline (at enrolment ± prior to Booster Nurse Clinic, if relevant), (*t*_2_) 3 months, (*t*_3_) 6 months, and (*t*_4_) 12 months.

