**Process outcomes**							
Completion of intervention component						**X**	
Clinical encounters at cancer centre							**X**
Referrals back to acute care							**X**
GP and specialist visits							**X**

*t*_1_ baseline, *t*_2_ 3 months, *t*_3_ 6 months, *t*_4_ 12 months

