### Concealment mechanism {16b}

Allocation sequence is implemented using sequentially numbered opaque, sealed envelopes. Envelopes are only accessed by the research nurse to randomise the patient once recruitment and baseline data has been collected.

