### Implementation {16c}

Allocation sequence is generated by a researcher not involved in recruitment or data collection. Patients are enrolled by a research nurse who collects baseline data prior to randomisation. Enrolling nurses assign participants to the intervention after baseline data collection.

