Patient experience of care as measured by the Picker Patient Experience 15 (PPE-15) questionnaire [30]. The PPE-15 highlights aspects of care that need improvement to monitor performance and care. It consists of 15 questions distributed to seven dimensions of care: respect, coordination, information/communication/education, physical comfort, emotional support, involvement of relatives, and transitions to community [31].Dietary behaviours, specifically usual vegetable intake and usual fruit intake, as measured by two short dietary questions from the National Nutrition Survey [32], which have been validated in the Australian population. Both questions discriminate between groups with significantly different fruit and vegetable intakes. In administering these questions, information about which foods are included as vegetables and fruits is provided and serve sizes are described.Physical activity as measured by the Active Australia Survey [33] which is designed to measure participation in leisure-time physical activity, and a single item from the International Physical Activity Questionnaire [34] will be used to measure sedentary behaviours.Financial toxicity as measured by the 11-item Comprehensive Score for financial Toxicity (COST)-Functional Assessment of Chronic Illness Therapy (FACIT) tool [35]. This tool is valid and reliable in measuring financial toxicity in patients with cancer [36].Adherence to clinical assessments including annual mammography, annual physical examination, and endocrine therapy as measured by hospital records.Emergency presentations and hospitalizations as recorded from hospital records.Satisfaction of care as measured by a 0–10 numerical analogue scale with 0 being the least satisfied and 10 being the most satisfied, supplemented with short, structured qualitative questions.Process outcomes, including completion of intervention components, as measured by completion of intervention materials such as SCPs and checklists, number and length of clinical encounters recorded from MBS data and hospital records, and barriers and facilitators to implementation as explored through semi-structured interviews with patient participants, their nominated carer, breast cancer nurses, GPs, and other healthcare providers including other nurses, and hospital- and community-based rehabilitation providers.Health resource utilisation assessing both health service use and participant out-of-pocket costs including MBS and PBS administrative data sets. These data inform participants’ utilisation of services that qualify under the MBS as well as medications dispensed under the PBS. It is planned that the economic evaluation may be reported separately from the main trial.

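### Patient experience of care (PPE-15) is a secondary outcome but is scheduled only at the pre-randomisation baseline, so no effect of EMINENT on it can be estimated

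*Protocol article*

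**What the plan says.** The abstract (Methods) states: "Secondary outcomes include patient experience, acceptance, and satisfaction of care". Section 18a repeats this in its list of secondary outcomes and gives the instrument: "Patient experience of care as measured by the Picker Patient Experience 15 (PPE-15) questionnaire". It describes 15 questions over seven dimensions, among them coordination, information and education, and transition to the community. It gives no assessment time.

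The time is given only in Table 3 (section 12). Under the secondary endpoints, the row "Patient experience of care" has one X, in the t1 column. The cells for t2 (3 months), t3 (6 months), t4 (12 months) and close-out are empty. The legend defines t1 as baseline.

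Two sections fix baseline relative to allocation. Section 16c says: "Patients are enrolled by a research nurse who collects baseline data prior to randomisation". Section 16b says: "Envelopes are only accessed by the research nurse to randomise the patient once recruitment and baseline data has been collected".

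Section 20a plans preliminary effect sizes for patient outcomes, by intention to treat, from generalised linear mixed models.

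**The concern.** An outcome has to be observed after allocation if it is to carry information about the intervention. As scheduled, the PPE-15 is handled like the demographic and clinical characteristics in the same table, which also have a single mark at t1. It is nevertheless labelled a secondary endpoint and falls within the effect estimates of section 20a.

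The PPE-15 dimensions of coordination, information and transition to the community correspond closely to the barriers that the Introduction and Discussion say the nurse-enabled model is meant to overcome. A pilot that is to supply preliminary effect sizes for a definitive trial would supply none for this outcome. Data not collected at the time cannot be recovered at analysis.

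**Working it through.** The protocol states no figure to reproduce for this outcome. The check is one of timing, followed by a short calculation of what the fix would give.

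**Step 1: column position.** Table 3 has seven time columns, in the order −t1, 0, t1, t2, t3, t4, tx. The patient experience row has all seven cells, and its only X is in the third, t1. The row "Health-related quality of life" has its first X in the same column and continues through t4. Neighbouring rows keep their own distinct patterns, so the row does not look shifted.

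**Step 2: post-baseline assessments by outcome (Table 3).**

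| Outcome | At t1 | At t2, t3, t4 |
|---|---|---|
| Health-related quality of life | yes | 3 |
| Diet | yes | 3 |
| Physical activity and sedentary behaviour | yes | 3 |
| Financial toxicity | yes | 2 (t3, t4) |
| Satisfaction of care | no | 1 (t4) |
| Acceptance of intervention | no | 1 (t4) |
| Patient experience (PPE-15) | yes | 0 |

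**Step 3: t1 relative to randomisation.** Sections 16b and 16c both put baseline collection before the envelope is opened. Table 3 prints t1 under its post-allocation heading, which conflicts with those sections. Even on that reading, a baseline value taken just after allocation would precede delivery of the intervention.

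**Step 4: what can be estimated.** Let Y be the PPE-15 score at t1. Because Y is fixed before allocation, randomisation gives E[Y | EMINENT] − E[Y | usual care] = 0 for any true effect of EMINENT. A mixed model fitted to t1 values alone has no parameter that represents an intervention effect.

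**Step 5: the possible extra assessment.** Section 8 defines t1 as "baseline (at enrolment ± prior to Booster Nurse Clinic, if relevant". The booster clinic is listed in Table 1 as an EMINENT component, offered where GP involvement is delayed by more than 3 months. If the PPE-15 were repeated there, some post-randomisation values would exist, but only in a selected part of one arm. The number scheduled in the control arm remains 0 of 30, so there is still no randomised comparison.

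**Step 6: precision if the PPE-15 were added at 12 months.** For an unadjusted two-sample comparison in SD units, the 95% half-width is t(0.975, 2n − 2) × √(2/n).

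- n = 30 per arm (section 14): t(0.975, 58) = 2.002 and √(2/30) = 0.258, giving 0.517 SD.
- n = 24 per arm (20% loss, an assumption, since the protocol states no attrition rate): t(0.975, 46) = 2.013 and √(2/24) = 0.289, giving 0.581 SD.

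**The case against.** The strongest case on the other side accepts the reading of the table and disputes its weight.

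- **Severity.** This is a pilot, not aimed at hypothesis testing. Its feasibility outcomes are recruitment and acceptability, and its primary endpoint, FACT-B, is measured at all four timepoints. Patients' views of care are still gathered after randomisation through satisfaction and acceptance at 12 months and through interviews with intervention participants. All this is true, and it limits the harm to one secondary outcome. Satisfaction is a separate outcome, however, scored on a 0–10 scale with short qualitative questions, and does not measure the PPE-15 dimensions. The interviews have no control arm.
- **An editing slip.** Table 3 has a mislabelled heading over t1, so a mark may have been left out of the published table. This cannot be excluded. The published schedule would still need correcting.
- **The booster repeat of baseline.** This makes an unqualified count of zero post-intervention values out of 60 too absolute. The qualification stands, but it does not supply a control comparison.
- **The precision figures.** They describe a hypothetical measurement and ignore the planned covariate adjustment. That is fair. They show only what the fix would yield and are not the size of the defect.
- **Intended as a description of prior care.** The article describes the instrument as showing where care needs improving, which would suit a baseline-only use. In that case the label of secondary outcome is wrong.

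**Conclusion.** The concern holds. As written, the PPE-15 has one scheduled assessment, before randomisation, and none at 3, 6 or 12 months or at close-out. No control-arm value exists after allocation, so no between-arm effect on patient experience can be estimated, and the article promises a secondary result that its schedule cannot deliver.

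The conclusion rests on Table 3 being as the authors intended and on sections 16b and 16c governing the timing of baseline. It does not depend on any assumed effect size, SD or attrition rate. The consequence is confined to this secondary outcome, and the trial as a whole remains valid.

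**What to change.** Add the PPE-15 at t4 (12 months) for both arms in Table 3, next to satisfaction and acceptance, and retain the t1 value as the baseline covariate in the model of section 20a. Participants not yet at 12 months would then contribute to an estimable comparison.

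The cost is one row of Table 3, a change to the REDCap schedule, 15 more items at an assessment already planned, and a minor ethics amendment.

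If Table 3 merely omits a mark that is in the full protocol, correct the table. If baseline-only measurement was intended, move the PPE-15 to participant characteristics and remove it from the secondary outcomes in the abstract, section 18a and Table 3. That resolves the inconsistency but gives up the estimate.

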**Participant characteristics**							
Demographics			**X**				
Clinical characteristics			**X**				
**Process outcomes**							
Completion of intervention component						**X**	
Clinical encounters at cancer centre							**X**
Referrals back to acute care							**X**
GP and specialist visits							**X**

*t*_1_ baseline, *t*_2_ 3 months, *t*_3_ 6 months, *t*_4_ 12 months

### Participant timeline {13}

### Sample size {14}

In this pilot study, we will recruit 30 patients per arm in order to provide initial insights into the intervention feasibility and protocol as well as preliminary effect size estimates. The aim of this study is not hypothesis testing, and the power level is therefore not a valid consideration for sample size [28, 29]. The sample size for this study (*n* = 60) falls within the range of sample size recommendations for pilot studies of this nature [28, 29].

### Recruitment {15}

Participants are recruited through the hospital cancer outpatient clinics and therapy units. Research nurses and designated health professionals identify potential participants. Potential participants are reviewed by a member of the treating team and asked if they would like to be approached by a research nurse or designated health professionals for consent to participate in the study. Participants are given as much time as possible to consider their participation and are encouraged to take the information away and discuss participation in the trial with family, friends, and their GP if they so wish to. Participants are also encouraged to ask the research nurses, their treating doctors, or nursing staff any questions in relation to their participation.

## Assignment of interventions: allocation

### Sequence generation {16a}

Computer-generated random numbers are used to allocate participants in a 1:1 ratio by a researcher not involved in recruitment, intervention implementation, or data collection. Randomisation is blocked using random permuted blocks of eight and four to ensure that the groups are balanced periodically within stratification groups. Stratification groups include patients who have received (1) surgery only, (2) surgery and radiation only, (3) surgery and chemotherapy ± radiation and are Her2 negative, and (4) surgery and chemotherapy ± radiation and are Her2 positive. These stratification groups were chosen, with clinician input, to allow learnings for patients with different treatment pathways with different follow-up needs to inform the future definitive trial.

### Concealment mechanism {16b}

Allocation sequence is implemented using sequentially numbered opaque, sealed envelopes. Envelopes are only accessed by the research nurse to randomise the patient once recruitment and baseline data has been collected.

### Implementation {16c}

Allocation sequence is generated by a researcher not involved in recruitment or data collection. Patients are enrolled by a research nurse who collects baseline data prior to randomisation. Enrolling nurses assign participants to the intervention after baseline data collection.

## Assignment of interventions: blinding

### Who will be blinded {17a}

After assignment to the intervention, only outcome assessors are blinded to group allocation. Where participants opt to complete their data collection by phone, they are advised not to reveal their group allocation to the outcome assessor. Due to the nature of the intervention, no participants or treating clinicians are blinded.

### Procedure for unblinding if needed {17b}

No unblinding procedures required as only outcome assessors and data analysts are blinded.

## Data collection and management

### Plans for assessment and collection of outcomes {18a}

Patient-reported outcomes are self-administered using online surveys or administered in person or via telephone with an outcome assessor trained in the administration of the study instruments. The description of study instruments is listed in Table 3.

The primary outcome is HRQoL as measured by Functional Assessment of Cancer Therapy—Breast Cancer (FACT-B) [26]. This validated and reliable instrument is well-used in cancer survivors undergoing and beyond treatment [27], and it captures key domains of HRQoL and key symptoms that are relevant to the EMINENT intervention.

The secondary outcomes are listed below:
Patient experience of care as measured by the Picker Patient Experience 15 (PPE-15) questionnaire [30]. The PPE-15 highlights aspects of care that need improvement to monitor performance and care. It consists of 15 questions distributed to seven dimensions of care: respect, coordination, information/communication/education, physical comfort, emotional support, involvement of relatives, and transitions to community [31].Dietary behaviours, specifically usual vegetable intake and usual fruit intake, as measured by two short dietary questions from the National Nutrition Survey [32], which have been validated in the Australian population. Both questions discriminate between groups with significantly different fruit and vegetable intakes. In administering these questions, information about which foods are included as vegetables and fruits is provided and serve sizes are described.Physical activity as measured by the Active Australia Survey [33] which is designed to measure participation in leisure-time physical activity, and a single item from the International Physical Activity Questionnaire [34] will be used to measure sedentary behaviours.Financial toxicity as measured by the 11-item Comprehensive Score for financial Toxicity (COST)-Functional Assessment of Chronic Illness Therapy (FACIT) tool [35]. This tool is valid and reliable in measuring financial toxicity in patients with cancer [36].Adherence to clinical assessments including annual mammography, annual physical examination, and endocrine therapy as measured by hospital records.Emergency presentations and hospitalizations as recorded from hospital records.Satisfaction of care as measured by a 0–10 numerical analogue scale with 0 being the least satisfied and 10 being the most satisfied, supplemented with short, structured qualitative questions.Process outcomes, including completion of intervention components, as measured by completion of intervention materials such as SCPs and checklists, number and length of clinical encounters recorded from MBS data and hospital records, and barriers and facilitators to implementation as explored through semi-structured interviews with patient participants, their nominated carer, breast cancer nurses, GPs, and other healthcare providers including other nurses, and hospital- and community-based rehabilitation providers.Health resource utilisation assessing both health service use and participant out-of-pocket costs including MBS and PBS administrative data sets. These data inform participants’ utilisation of services that qualify under the MBS as well as medications dispensed under the PBS. It is planned that the economic evaluation may be reported separately from the main trial.

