### Additional consent provisions for collection and use of participant data and biological specimens {26b}

Consent to access Medicare and Pharmaceutical Benefits Scheme (PBS) data on service use that qualifies under the Medicare Benefits Schedule (MBS) will be obtained, including relevant claims details (date of service, Medicare item number, and description) and costs details.

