**Shared follow-up care** *Mode: face to face or telehealth*	Cancer specialist, GP, and Specialist Cancer Nurse^a^ and patient	• Cancer specialist reviews patient, orders mammogram, and completes full physical examination every 6 months for 2 years post-diagnosis, then every 12 months up to 5 years post-diagnosis • GP reviews patient as per survivorship care plan at least every 12 months (e.g. for general health and comorbidity management, chronic disease management planning, psychosocial screening, management of cancer treatment toxicities and cancer-related symptoms, allied health referrals) • GP contacts nurse interventionist with any patient concerns

^a^Medical Oncology Clinical Nurse Consultant, Breast Care Nurse, or McGrath Breast Care Nurse

^b^Offered to patients who have delays in GP involvement greater than 3 months (up to 18 months)

^c^Offered to patients who have completed chemotherapy and/or are scheduled to receive aromatase inhibitor, or have completed surgery and radiotherapy

After enrolment, participants who have completed chemotherapy and radiotherapy or those who will receive aromatase inhibitor will participate in a 20-min telehealth cancer pharmacist consultation for medication reconciliation and education prior to Specialist Nurse consultation.

A 30–60-min consultation with a Specialist Cancer Nurse is then conducted to provide a treatment summary, the shared follow-up care appointment schedule, and survivorship patient education (including the survivorship booklet on *Living Well After Cancer* published by Cancer Council Australia [14]) and to co-develop a draft Survivorship Care Plan (SCP). The SCP includes up to three SMART (Specific, Measurable, Achievable, Realistic, and Timely) goals that are developed by the nurse and patient in partnership using motivational interviewing and self-efficacy techniques. Due to the recent COVID-19 pandemic, where there are delays of 3–18 months before GP involvement, a second ‘booster’ Specialist Cancer Nurse consultation is offered to patients to update the SCP. The treatment summary and draft SCP is provided to the GP.

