Within 4 weeks of the Specialist Cancer Nurse consultation, a 5–30-min case conference between the Specialist Cancer Nurse and the patient’s nominated GP is completed to communicate the treatment summary and shared follow-up care schedule and to finalise the SCP and negotiate the GP’s role in facilitating the SCP goals. The GP may propose changes or express if they are not willing to take part in specific care activities outlined in the SCP. The finalised SCP is then filed in the patient’s medical records and provided to the patient and the GP.

The shared, follow-up care schedule consists of 6-monthly patient appointments with a cancer centre specialist and annual appointments with the GP for 2 years post-diagnosis. Following this, the schedule consists of alternating 6 monthly appointments with a cancer centre specialist and GP for up to 5 years post-diagnosis. At 5 years post-diagnosis, patients are discharged to the care of the GP, as per usual care. The GP appointments will focus on reviewing the SCP; promoting general health; primary prevention, screening, and management of comorbidities; psychosocial health; cancer treatment toxicities; cancer-related symptoms; chronic disease management planning; and allied health referrals. The GP has direct telephone access to the Specialist Cancer Nurse in case of concerns or escalation for acute care review. The cancer centre specialist appointments focus on surveillance activities such as physical examination and imaging (i.e. annual mammogram).

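### Endocrine-therapy adherence is taken from hospital records alone, although the PBS dispensing data already obtained would measure it better in both arms

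*Protocol article*

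**What the plan says.** Section {18a} of the protocol article lists as a secondary outcome "Adherence to clinical assessments including annual mammography, annual physical examination, and endocrine therapy as measured by hospital records". Hospital records are the only source named. Table 3 places this outcome at close-out.

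The trial also obtains administrative claims. Section {26b} provides for "Consent to access Medicare and Pharmaceutical Benefits Scheme (PBS) data on service use", including date, item number, description and cost. Section {18a} says these data inform "medications dispensed under the PBS", but assigns them to health resource utilisation. MBS data are also used, with hospital records, to count clinical encounters. Neither MBS nor PBS data are linked to adherence.

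On who does what in the EMINENT arm, Table 1 in section {11a} states "Cancer specialist reviews patient, orders mammogram, and completes full physical examination every 6 months for 2 years post-diagnosis", then yearly up to 5 years. The text of {11a} gives, after the first 2 years, "alternating 6 monthly appointments with a cancer centre specialist and GP for up to 5 years post-diagnosis". The GP's tasks include "management of cancer treatment toxicities and cancer-related symptoms". Endocrine prescribing is not listed among them.

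**The concern.** Endocrine therapy is continuing medication, so adherence depends on whether supply continues after the prescription. A source that records the clinician's intention can count a patient who has stopped as adherent, and can miss a patient whose treatment continues without a hospital entry. The trial collects dispensing data but does not use them for the one outcome that asks this question.

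The stake is what the pilot passes on. Section {14} says it should give preliminary effect size estimates, and the abstract says the results will inform a definitive trial. Section {22} plans no adverse event reporting, so adherence is one of the few indicators of whether treatment continues under shared care. If the measure is insensitive, similar figures in the two arms would say little.

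**Working it through.** The article states no adherence rate, so there is no figure to reproduce. The check takes each component against its source, then shows how recording error would act.

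**1. Components against source**

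- *Physical examination and mammography.* Under {11a} both stay with the cancer specialist in EMINENT: 6-monthly for 2 years after diagnosis, then at least yearly. Hospital records are a natural source, and the schedule implies arm-specific loss near 0. A mammogram done elsewhere could be missed in either arm; the article does not say how often.
- *Endocrine therapy.* Hospital records are the only source named. PBS data would show dispensing for every consenting participant, whichever arm they are in.

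**2. Same recording error in both arms**

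Let p be true adherence, f the share of adherent patients not recorded as such, and g the share of non-adherent patients recorded as adherent (prescribed, not dispensed).

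Recorded adherence = p(1 − f) + (1 − p)g.

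With the same f and g in both arms, a true difference D is recorded as D(1 − f − g). The documents give neither f nor g. Assumed values:

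- f = g = 0.1: 1 − 0.1 − 0.1 = 0.8, so 80% of D remains.
- f = g = 0.3: 1 − 0.3 − 0.3 = 0.4, so 40% remains.
- f = g = 0.5: 1 − 0.5 − 0.5 = 0, so nothing remains.

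**3. Recording error in one arm only**

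Take the same p in both arms, g = 0, and under-recording f in one arm only. The false difference has size p × f and counts against that arm. The Wald 95% half-width with 30 per arm ({14}), writing a = p(1 − f), is 1.96 × √[p(1 − p)/30 + a(1 − a)/30].

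Example: p = 0.8 and f = 0.3 give a = 0.56. The false difference is 0.8 × 0.3 = 0.24. The half-width is 1.96 × √(0.16/30 + 0.2464/30) = 0.228.

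False difference / half-width, in percentage points (p and f assumed):

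| p | f = 0.1 | f = 0.2 | f = 0.3 | f = 0.5 |
|---|---|---|---|---|
| 0.7 | 7 / 23.8 | 14 / 24.2 | 21 / 24.3 | 35 / 23.7 |
| 0.8 | 8 / 21.5 | 16 / 22.4 | 24 / 22.8 | 40 / 22.6 |
| 0.9 | 9 / 17.7 | 18 / 19.3 | 27 / 20.3 | 45 / 20.8 |

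At f = 0.2 the artefact stays within the half-width in all three rows. At f = 0.3 it exceeds it for p = 0.8 and 0.9, and at f = 0.5 in every row. Not all 30 per arm will be on endocrine therapy, so the real half-widths are wider.

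**4. Which arm would be under-recorded?**

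The design points both ways. In EMINENT, treatment toxicities may be managed by the GP, which could leave less in the hospital record. But EMINENT alone adds a cancer pharmacist consultation with medication reconciliation, offered among others to those due an aromatase inhibitor, and a nurse-led care plan filed in the medical record. Control follow-up is not standardised. The sign cannot be determined from the article.

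**The case against.** The strongest objection is that little here depends on arm. Examination and mammography stay with the specialist, no passage moves endocrine prescribing to the GP, and community dispensing would be unseen in both arms. EMINENT may even be better documented. The outcome is one of many secondary ones in a 60-patient pilot that disclaims hypothesis testing. The exact adherence definition may also sit in the full protocol.

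Most of this stands, and it rules out several stronger readings:

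- A reader might infer that care shared with GPs is invisible to the trial. It is not: {18a} counts encounters from MBS data as well as hospital records, and Table 3 lists GP and specialist visits.
- A reader might take "The GP appointments will focus on reviewing the SCP" to mean that surveillance moves to general practice, so that mammography and examination go unrecorded in EMINENT. The same part of {11a} keeps both with the specialist.
- A reader might expect EMINENT to look less adherent by some definite amount. The documents support neither the direction nor a size; any such figure only restates an assumed gap in recording.

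The objection does not reach the choice of source. The article does not leave it open: it names hospital records and describes a dispensing source used for something else. That would be a weakness even if both arms were recorded identically.

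**Conclusion.** The point holds for endocrine therapy only. Hospital records are a poor measure of continued treatment in both arms, and the trial already obtains a better one. Recording that differs by arm is possible, in an uncertain direction.

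The size is unknown. The illustrations assume true adherence of 70% to 90% and recording errors of 10% to 50%, none of which comes from the documents. They show that equal errors would shrink a real difference, and that an imbalance of about 30% or more could rival the sampling error of 30 per arm. The conclusion also assumes that the hospital record does not itself hold community dispensing, which the article does not address.

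The consequence is modest. The primary endpoint is unaffected, no hypothesis test is planned, and the article states no progression rule based on adherence. The change is still worth making because it is cheap and the pilot is meant to inform a larger trial.

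**What to change.** In {18a}, define endocrine-therapy adherence from PBS dispensing (for example, the proportion of days covered over 12 months), alongside hospital records, with the same definition and window in both arms. Keep hospital records as the source for mammography and physical examination; MBS claims may supplement them for mammograms done elsewhere, again in both arms.

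The cost is a wording change and some coding of data already requested. GP practice records are not needed. The downside is coverage: only participants who consent to MBS/PBS release contribute, and {18b} lets those who withdraw also end passive collection of these data. Report participants without PBS data separately, by arm, using hospital records alone. Dispensing is still not proof that the medicine was taken, and the report should say so.
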